### Secondary study objectives

Additionally, we will investigate quality of life as reflected by psychological burden, and cost-effectiveness of the first trimester 3D VR ultrasound. Both factors will be compared between the intervention and control group. Finally, patient and ultrasonographer perspectives will be studied.

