### Procedures, recruitment and randomization

Eligible women will be identified by the participating hospital. Referring healthcare providers will be contacted to ensure timely referral (< 14 + 0 weeks’ GA). Women eligible for the trial will be counseled before participation by medical doctors or research nurses in accordance to the ‘Good Clinical Practice (GCP)’ guidelines [30]. Written informed consent will be obtained (Supplement 1 and 2).

Following participation, the participant will be entered in a web-based computerized database (ALEA®) for randomization. After complete registration in the online randomization database, the allocation will be shown. The online randomization software is available at all times. Randomization will be performed using block randomization with random block samples of *N* = 4–16. Due to the nature of the intervention, this will not be a blinded study.

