### Questionnaires

All participants will fill out questionnaires on health related quality of life. The following validated questionnaires will be sent at fixed time points in pregnancy: the MOS 36-item Short Form Health Survey (SF-36), the Hospital Anxiety and Depression Scale (HADS), the Spielberger State-Trait Anxiety Inventory (STAI) and a visual analogue scale (VAS) for wellbeing [33–35]. The four questionnaires will be sent digitally to the participants on the day of inclusion, the first trimester 3D VR ultrasound (or after 13 weeks GA for the control group), the second trimester 2D ultrasound and 4 weeks after the estimated due date, respectively. The answers will be recorded on a secure webserver on the Erasmus MC premises.

Direct healthcare costs will be recorded using the iMTA Medical Consumption Questionnaire (iMTA MCQ) [36]. All significant costs and health effects on the short term up to 4–6 weeks after delivery or termination of pregnancy will be considered. Therefore, these questionnaires will be sent at 20 and 32 weeks GA and 4 weeks after the estimated due date. In case of an intra-uterine fetal demise or termination of pregnancy during the trial, women will be sent specifically adjusted questionnaires.

Participant perspective on the 3D VR ultrasound will be evaluated with an in-house developed questionnaire. This survey includes questions about the value of ultrasound imaging in the first trimester and personal perception of the added value of 3D VR. This questionnaire will be sent after the first trimester 3D VR ultrasound or around 13 weeks GA in the control group. This questionnaire will be validated in a subset of 50 participants.

Ultrasonographer opinion of both the first trimester 2D and the 3D VR ultrasound will be evaluated by another in-house developed questionnaire. More specifically, the additional value of the 3D VR in terms of patient understanding, counseling and detection of anomalies will be examined.

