Secondary outcome measures will be health-related quality of life and cost-effectiveness of first trimester 3D VR ultrasound from a societal perspective. Health related quality of life will be expressed in physical, emotional and social functioning. Quality Adjusted Life Years (QALY’s) will be calculated from a maternal perspective, derived from the validated questionnaires. Actual expenses during the study will be measured using the standard costs as stated by the Dutch costing guidelines [37]. For each strategy (control versus intervention) the quality of life will be computed as well as the average costs per patient. The incremental cost-effectiveness ratio (ICER) will be calculated by dividing the difference in costs by the difference in quality of life. It represents the extra costs required to obtain one QALY. Furthermore, the cost per anomaly detected will be estimated. The cost-effectiveness analysis will span a period from approximately 8 weeks of gestation, when regular obstetric care starts, up to approximately 2 months beyond the estimated date of delivery. In this analysis, costs and effects will not be discounted due to a short time frame. Indirect costs will not be accounted for. The costs will be presented in Euros. The index year will be 2018.

Additionally, through a newly implemented questionnaire, the perspective of both patient and ultrasonographers on the new 3D VR modality will be surveyed. The participant perspective of the first trimester 3D VR ultrasound group (=intervention) will be compared to second trimester 2D ultrasound (=control).

An overview of all patients’ characteristics and data is shown in Table 1.

**Table 1 Tab1:** Patient characteristics collected within the VR FETUS study. Details of data collection form the first trimester up to 6 weeks after delivery are depicted

**Maternal Characteristics**	**Outcome**
Age	Years (mean ± SD)
Ethnicity	Dutch/Other western/Non-western
Level of education	Low, middle, high
Postal code	
Medical history	Unremarkable/Diabetes/Epilepsy/Other
Obstetrical history	Parity, miscarriage, previous pregnancy with congenital anomaly
Family history	Unremarkable/family members with congenital anomaly
Marital status	Married/not married
Global household income	€0–20.000/€20.000–35.000/€35.000–65.000/>€65.000 annually
BMI	Kg/m^2^ (mean ± SD)
Alcohol use during first trimester	No/Yes: how many units per day?
Smoking during first trimester	No/yes: how many cigarettes per day

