#### Data-analysis

Data will be analyzed according to the intention-to-treat principle. No interim analysis will be performed.

Statistical analysis will be performed using IBM SPSS (SPSS Inc., Chicago, IL, USA) and R Studio (The R Foundation for Statistical Computing). Descriptive statistics will be used to describe the baseline characteristics of both the control and intervention group (e.g. maternal characteristics such as ethnicity, age, smoking status, Body-Mass Index (BMI) and family history, pregnancy characteristics such as parity and pregnancy outcome, medication use such as antidepressants and antiepileptic medication). Categorical data will be presented by number of participants (%) and numerical data by median (interquartile range). These baseline characteristics will be compared between the arms using Mann Whitney U-test for continuous variables and chi-squared test for categorical variables. When the expected count in 20% or more of the cells of the cross table for the categorical variables is 5 or lower or if any cell is empty an exact test will be used instead. A significance level (alpha) of 0.05 will be used. No multiplicity correction will be applied.

The economic analysis will be performed from the societal perspective. The costs and quality of life will be compared between the two diagnostic regimens. Descriptive statistics will be used to describe the outcomes of quality of life analysis (control arm versus intervention arm).

Ultrasound is considered safe in pregnancy, therefore a data monitoring committee is not required [43]. Yearly reports will be sent to the ethics committee on the progress of the trial. When major modifications to the protocol are made, all people involved will be informed.

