Some challenges remain. The introduction of a first trimester ultrasound examination will necessitate an additional prenatal visit, as well as expertise and training of staff. This might increase healthcare costs. This study will add new understanding on maternal psychological functioning throughout pregnancy in relation to prenatal ultrasound. Ideally, we would use structured interviews. However, due to the size of the study this was not a possibility. Instead we chose to use validated questionnaires to investigate maternal stress and anxiety.

Some organ systems are not yet fully developed in the first trimester or are too small to be visualized in detail. As an example, one can state that it is not possible to detect all or a large proportion of fetal cardiac and brain anomalies in early pregnancy. Therefore, second trimester ultrasound examination cannot be omitted, and has to be used in addition to first trimester ultrasound.

From a clinician’s point of view, the first trimester ultrasound should be studied regarding its additional value of diagnostic performance. Rather than comparing first and second trimester ultrasound examination, the performance should be based on the combination of first and second trimester. We expect that first trimester detection will show an improvement in the clinical care of participants and lead to significant improvement in their quality of life. Furthermore, a second trimester ultrasound examination will show the development of a congenital anomaly over time. Parents’ decision for continuation of the pregnancy is likely to be affected by this. The second trimester ultrasound is indispensable, therefore we will study the combined first and second trimester ultrasound examination compared to the second trimester only.

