This study will provide the highest level of evidence in the evaluation of first trimester 3D VR ultrasonograhpy in a high risk population concerning quality of life and cost-effectiveness. Only with a randomized controlled trial, like this study, the additional value of the 3D VR desktop can be examined in terms of improved diagnostic yield of regular first trimester 2D ultrasound and patients perspectives. If this new modality proves to be cost-effective or shows to improve quality of life, it should be offered in addition to the second trimester 2D ultrasound examination. The wider implications of the results will give policymakers and healthcare professionals an educated choice as whether to add first trimester ultrasound for detection of congenital anomalies in a high risk group as part of routine care.

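### Quality of life is a between-arm objective and is treated as enough to justify offering the scan, but the only method named for it is description by arm, with no interval, test or use of the inclusion scores

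*Protocol article*

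**What the plan says.** The Secondary study objectives name quality of life (as psychological burden) and cost-effectiveness, and state: "Both factors will be compared between the intervention and control group". The Discussion expects that first trimester detection will "lead to significant improvement in their quality of life", and later says: "If this new modality proves to be cost-effective or shows to improve quality of life, it should be offered".

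The Data-analysis section has two sentences on the matter. The first announces a comparison: "The costs and quality of life will be compared between the two diagnostic regimens". The second gives the method: "Descriptive statistics will be used to describe the outcomes of quality of life analysis (control arm versus intervention arm". The Mann-Whitney, chi-squared and exact tests in that section are assigned to baseline characteristics. Under Outcome measurements, a difference also appears in the economic analysis: "The incremental cost-effectiveness ratio (ICER) will be calculated by dividing the difference in costs by the difference in quality of life".

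Four instruments are used (SF-36, HADS, STAI and a wellbeing VAS). Table 1 schedules each at inclusion, at the intervention or 13 weeks, at 20 weeks and after the due date. According to the Questionnaires section, the forms "will be sent digitally to the participants on the day of inclusion" and at the later occasions. On randomization, the Procedures section says: "After complete registration in the online randomization database, the allocation will be shown". It adds that the study is not blinded.

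**The concern.** The stated method falls short of the stated conclusion. To say that a modality improves quality of life, one needs the size of the between-arm difference and its uncertainty. Means or medians by arm supply neither a margin of error nor a basis for separating a real difference from chance. Here the conclusion matters, because the word *or* in the Discussion lets quality of life carry the recommendation without cost-effectiveness.

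Two features make this worse. First, four instruments at three follow-up occasions are available and none is singled out, so the favourable claim has no defined target. Second, every woman is scheduled to give an inclusion score, the natural covariate, but the plan gives it no role. That score is also unprotected: it comes from a digital form sent on the inclusion day of an open-label trial, and nothing requires it to be answered before the woman can learn her arm.

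**Working it through.** **Setting the passages side by side.**

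| Place | What it requires or provides |
|---|---|
| Secondary study objectives | a comparison between arms |
| Discussion | an expected significant improvement; improvement alone sufficient to offer the scan |
| Outcome measurements | a point difference in quality of life, as denominator of the ICER |
| Data-analysis | a comparison announced; method given as descriptive statistics by arm |

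A crude difference is therefore planned. What is missing between the last row and the first two is a measure of uncertainty for that difference.

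**Is a proper estimate feasible?** The article gives no effect size, SD, correlation, response rate or sample size for quality of life, so there is no planned figure to reproduce. The total of 2,800 was set for the detection endpoint and serves here only as a count of women. Inputs:
- n = 2,800 / 2 = 1,400 per arm (1:1 allocation assumed; the ratio is not stated)
- r, the correlation between inclusion and follow-up score: assumed 0 to 0.7
- response: assumed 50% to 100%

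In SD units:
- 95% CI half-width = 1.96 × √(1 − r²) × √(2/n)
- difference detectable with 80% power = (1.96 + 0.84) × √(1 − r²) × √(2/n)

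For n = 1,400, √(2/1,400) = 0.0378. Unadjusted (r = 0), the half-width is 1.96 × 0.0378 = 0.074. At r = 0.5, √0.75 = 0.866 and the half-width is 0.064.

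| Response | r | Half-width (SD) | Detectable difference (SD) |
|---|---|---|---|
| 100% | 0 | 0.074 | 0.106 |
| 100% | 0.5 | 0.064 | 0.092 |
| 100% | 0.7 | 0.053 | 0.076 |
| 50% | 0 | 0.105 | 0.150 |
| 50% | 0.5 | 0.091 | 0.130 |
| 50% | 0.7 | 0.075 | 0.107 |

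Even at 50% response, the interval is narrow enough to be informative.

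**Why the order of steps matters once baseline is used.** Suppose that knowing the arm shifts the inclusion score by b SD. Adjusting for that score then moves the effect estimate by about r × b in the opposite direction. With an assumed b = 0.1, this is 0.03 SD at r = 0.3, 0.05 at r = 0.5 and 0.07 at r = 0.7. These shifts are of the same order as the half-widths above. An unadjusted follow-up comparison would not carry this bias, so the adjustment and the ordering rule belong together.

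**Which occasion suits a single named comparison.** In the intervention arm the first trimester form is sent on the day of the 3D VR scan; in controls it is sent after 13 weeks and is tied to no scan. The postnatal form is dated 4 weeks after the due date under Questionnaires and 6 weeks in Table 1. The second trimester form is tied to the same kind of visit in both arms.

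**The case against.** The strongest reply has four parts.

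1. *A comparison is planned.* This stands. Data-analysis announces one and the ICER needs a difference. A reader might infer from the descriptive sentence that the arms will not be compared at all; the documents do not support that.

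2. *An unadjusted difference in a randomised trial is valid.* This also stands. A reader might infer that the trial could yield no valid effect estimate without a baseline model. It could; adjustment mainly buys precision, and the gain is modest (0.074 to 0.064 SD at r = 0.5).

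3. *A journal article leaves models, covariates and lead scales to the analysis plan.* This is correct as far as it goes, and the absence of a named model would not be a finding on its own. But the article is not silent: it states a method, and that method does not support what the Discussion proposes to conclude.

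4. *The Discussion sentence is not a prespecified decision rule, and the order of same-day steps is operational detail.* Both are partly right. Detection is the primary outcome, and the sentence is a conditional remark. It still tells policymakers what should follow from an improvement. On timing, a reader might infer that the baseline is contaminated by knowledge of allocation. The documents only leave that possible; they do not say which step comes first.

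A reader might also count scales and visits and compute a familywise false-positive rate. No such figure belongs here: a descriptive plan runs no such tests, the number of subscales would be the reader's choice, and repeated overlapping scales in the same women are not independent.

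**Conclusion.** The point holds as a mismatch between a stated method and a stated conclusion. As written, the plan would give summaries by arm and a crude difference for the ICER, and neither can show that the modality improves quality of life. It concerns a secondary outcome and does not touch the detection analysis, but it is worth correcting because the Discussion lets that outcome alone justify offering the scan.

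The numbers rest on assumptions absent from the documents: 1:1 allocation with 1,400 per arm, the response rate, and the inclusion-to-follow-up correlation. Over the range examined, the 95% CI half-width lies between 0.053 and 0.105 SD. The risk to the inclusion score is a possibility that the text leaves open, not an event that it describes.

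**What to change.** - **Data-analysis.** Replace the descriptive sentence with a between-arm difference and 95% CI for each scale, adjusted for the inclusion score (ANCOVA or a repeated-measures mixed model) and analysed by intention to treat. State how the adjusted questionnaires sent after fetal demise or termination enter this analysis.
- **Discussion.** Tie the statement about improved quality of life to one named scale at one occasion on which both arms are surveyed alike, for example the second trimester scan form. Avoid the first trimester form for this purpose. Label the other scales and occasions as supportive.
- **Procedures and Questionnaires.** Require the inclusion questionnaire to be completed before allocation is displayed.

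The cost is some wording and one rule on the order of steps. No new data are needed. The downside is a short delay before randomization. For women already enrolled, the completion time of the inclusion form could be compared with the time of allocation, if both were recorded.

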## Discussion

This is the first randomized controlled trial designed to detect anomalies in the first trimester using 3D VR ultrasonography, with longitudinal follow-up in pregnancy. One previous study has shown a high sensitivity for the detection of structural anomalies in the first trimester using 3D VR and a trend towards improved detection rates [16]. 3D VR may especially improve the detection of surface anomalies in the first trimester [20]. Timely detection of major congenital malformations will provide women at risk with additional time to perform (genetic) testing as well as more time to consider continuation or termination of pregnancy. In current Dutch practice even women from the high risk population are only offered a second trimester anomaly scan. In the high risk group an additional first trimester ultrasound examination may be beneficial since there will be an increased prevalence of anomalies. Furthermore, the absence of a major anomaly following a first trimester 3D VR ultrasound examination could offer earlier reassurance and reduce anxiety in pregnant women. Overall, we hypothesize this will improve cost-effectiveness and patient quality of life.

This study has several strengths. The use of a standardized examination protocol will improve the detection of fetal anomalies. Recent studies have shown increased detection rate of anomalies when a standardized ultrasound protocol is used compared to a strategy that consists of a global fetal survey [6]. Also, transvaginal ultrasound or the combination of transvaginal and transabdominal ultrasound may increase the detection of anomalies in the first trimester compared to only using a transabdominal approach. This is especially true in case of maternal obesity. Detection of anomalies will be further improved by the limited filtering of the ultrasound data by the 3D VR system, which can enhance fetal surface details and thus improve the examination of limbs and face. This technique also provides recognizable and identifiable ‘holograms’ for the future parents.

Some challenges remain. The introduction of a first trimester ultrasound examination will necessitate an additional prenatal visit, as well as expertise and training of staff. This might increase healthcare costs. This study will add new understanding on maternal psychological functioning throughout pregnancy in relation to prenatal ultrasound. Ideally, we would use structured interviews. However, due to the size of the study this was not a possibility. Instead we chose to use validated questionnaires to investigate maternal stress and anxiety.

Some organ systems are not yet fully developed in the first trimester or are too small to be visualized in detail. As an example, one can state that it is not possible to detect all or a large proportion of fetal cardiac and brain anomalies in early pregnancy. Therefore, second trimester ultrasound examination cannot be omitted, and has to be used in addition to first trimester ultrasound.

From a clinician’s point of view, the first trimester ultrasound should be studied regarding its additional value of diagnostic performance. Rather than comparing first and second trimester ultrasound examination, the performance should be based on the combination of first and second trimester. We expect that first trimester detection will show an improvement in the clinical care of participants and lead to significant improvement in their quality of life. Furthermore, a second trimester ultrasound examination will show the development of a congenital anomaly over time. Parents’ decision for continuation of the pregnancy is likely to be affected by this. The second trimester ultrasound is indispensable, therefore we will study the combined first and second trimester ultrasound examination compared to the second trimester only.

This study will provide the highest level of evidence in the evaluation of first trimester 3D VR ultrasonograhpy in a high risk population concerning quality of life and cost-effectiveness. Only with a randomized controlled trial, like this study, the additional value of the 3D VR desktop can be examined in terms of improved diagnostic yield of regular first trimester 2D ultrasound and patients perspectives. If this new modality proves to be cost-effective or shows to improve quality of life, it should be offered in addition to the second trimester 2D ultrasound examination. The wider implications of the results will give policymakers and healthcare professionals an educated choice as whether to add first trimester ultrasound for detection of congenital anomalies in a high risk group as part of routine care.

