**Methods:**

Women in the first trimester of a high risk pregnancy for a fetus with a congenital anomaly are eligible for inclusion. This is a randomized controlled trial with two intervention arms. The control group receives ‘care as usual’: a second trimester 2D advanced ultrasound examination. The intervention group will undergo an additional first trimester 2D and 3D VR ultrasound examination. Following each examination participants will fill in validated questionnaires evaluating their quality of life and healthcare related expenses. Participants’ and ultrasonographers’ perspectives on the 3D VR ultrasound will be surveyed. The primary outcome will be the detection of fetal anomalies. The additional first trimester 3D VR ultrasound examination will be compared to ‘care as usual’. Neonatal or histopathological examinations are considered the gold standard for the detection of congenital anomalies. To reach statistical significance and 80% power with a detection rate of 65% for second trimester ultrasound examination and 70% for the combined detection of first trimester 3D VR and second trimester ultrasound examination, a sample size of 2800 participants is needed.

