### Study design (see Fig. 3)

The design is a randomized controlled trial amongst women with a high risk for fetal anomalies in their pregnancy. Participants will be allocated to either the control or intervention group. In the control group, participants will receive ‘care as usual’ according to the Dutch national guidelines. The intervention group will undergo an additional first trimester 2D and 3D VR ultrasound examination. Both groups will be asked to complete questionnaires on wellbeing, quality of life, stress, anxiety and medical costs.

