### Control group

In the control group, participants will receive ‘care as usual’ which consists of a viability and pregnancy dating ultrasound examination around 10 weeks’ gestation followed by counseling for aneuploidy testing. Aneuploidy testing will be performed either via the first trimester combined test or via non-invasive prenatal testing (NIPT). Furthermore, an advanced ultrasound examination between 18 and 22 weeks’ gestation will be performed to screen for fetal anomalies. When indicated, additional ultrasound examinations will be planned, for instance fetal cardiac evaluation with a pediatric cardiologist.

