The 3D VR images will be extensively discussed with the future parents: this will take 30 min. At the end of the 3D VR evaluation and discussion, examiners A and B will compare their findings to reach agreement. In case of an anomaly, participants will be informed about the presence or suspicion of malformations by examiner B. Routine care will then be offered, consisting of an advanced anomaly scan by an experienced and independent sonographer.

In the absence of an anomaly, the intervention group will undergo a routine second trimester 2D ultrasound scan as part of ‘care as usual’.

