### Outcome measurements

The primary outcome will be the detection rate of fetal anomalies using first trimester 3D VR ultrasound in addition to the second trimester 2D ultrasound in a high risk population. Neonatal or histopathological examinations are considered the gold standard for the detection of congenital anomalies. For the detection rate analysis the sensitivity, specificity, positive and negative predictive values will be calculated for all ultrasound techniques for first trimester examination (i.e. 2D and 3D VR) in the intervention group and second trimester 2D examination in both groups (control group as well as intervention group). The detection rate of both first trimester examinations (i.e. 2D and 3D VR) will be compared. The detection rate of first trimester 2D will also be compared to the second trimester 2D ultrasound in the intervention group. In addition, we will assess the performance of the first trimester anomaly 2D and 3D VR ultrasound and the additional findings of the subsequent second trimester 2D ultrasound to gain a better insight into the whole diagnostic process.

The diagnostic performance of the first trimester ultrasound examination protocol will be compared to international ultrasound guidelines. Anatomical views (i.e. sagittal, transversal) according to our standardized protocol acquired per fetal structure will be evaluated as satisfactory or unsatisfactory. This assessment will be used to evaluate image quality per fetal structure and per modality, i.e. first trimester 2D and 3D VR. By doing this we will be able to examine the anatomical views which are essential to be included in the protocol, and the ones which are not. This evaluation will lead to optimization of the examination protocol in the future.

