### Quality

Sonographers will be trained to perform first trimester 3D VR ultrasound scans. As the first trimester ultrasound scan for fetal anomalies is currently not part of standard care in the Netherlands, the sonographers will receive additional training. They will all collect a portfolio comprising 5 complete ultrasound examinations, which will be reviewed by two experts. Unsatisfactory portfolios will be discussed with the sonographers in order to improve quality. When at least 5 high quality examinations of different patients have been collected, the sonographer can participate in the study.

To ensure quality of the first trimester ultrasound, all sonographers are asked to compile a new portfolio every 200 first trimester ultrasound scans.

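### The randomised contrast measures an added first-trimester 2D plus 3D VR examination, so its results cannot be reported as the effect of 3D VR

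*Protocol article*

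**What the plan says.** **What each arm receives.** Under Study design: "The intervention group will undergo an additional first trimester 2D and 3D VR ultrasound examination". Under Control group, controls have a viability and dating scan at about 10 weeks and counselling on aneuploidy testing, and then "an advanced ultrasound examination between 18 and 22 weeks’ gestation will be performed to screen for fetal anomalies". The Quality section confirms that "the first trimester ultrasound scan for fetal anomalies is currently not part of standard care in the Netherlands". Under Intervention group, examiner A performs the 2D scan and examiner B reads the 3D volumes in VR, each masked to the other. The VR images are discussed with the parents for 30 minutes. After that, "examiners A and B will compare their findings to reach agreement", and any anomaly is disclosed.

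**How the effect is labelled.** The abstract's Methods say: "The additional first trimester 3D VR ultrasound examination will be compared to ‘care as usual". In Outcome measurements the article defines the main endpoint as follows: "The primary outcome will be the detection rate of fetal anomalies using first trimester 3D VR ultrasound in addition to the second trimester 2D ultrasound". Later in that section it adds: "Secondary outcome measures will be health-related quality of life and cost-effectiveness of first trimester 3D VR ultrasound from a societal perspective". The primary objective uses the same label. In the sample size section, the 70% rate is for first-trimester 3D VR combined with second-trimester 2D; first-trimester 2D is not mentioned.

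**What is to be concluded.** The Discussion says: "Only with a randomized controlled trial, like this study, the additional value of the 3D VR desktop can be examined". The sentence goes on to give the terms: diagnostic yield relative to regular first-trimester 2D, and patients' perspectives. The next sentence says the new modality should be offered if it proves cost-effective or improves quality of life.

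**The concern.** The label and the design do not match. If the intervention arm does better, the cause may be the first-trimester 2D scan, the VR reading, the earlier timing, the extra visit, the 30-minute discussion, or any mixture of these. A reader of the primary outcome or of the closing Discussion would credit 3D VR.

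The decision at stake is whether to buy and staff a 3D VR desktop in addition to introducing a first-trimester anomaly scan. The randomised comparison informs the decision to introduce the combined examination. It does not say whether the VR part is needed.

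**Working it through.** **Step 1. Components by arm** (Study design, Control group, Intervention group, Quality).

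| Component | Intervention | Control |
|---|---|---|
| First-trimester 2D anomaly scan | yes | no |
| 3D VR reading and 30-minute discussion | yes | no |
| Second-trimester 2D scan | yes (routine if no anomaly found earlier) | yes |

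The first two rows always occur together.

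**Step 2. What the difference between arms contains.** Write Y(·) for the mean outcome (detection, quality of life or cost) under a set of examinations, T2 for the second-trimester scan, and VR for the VR reading with its discussion. Then

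Y(2D + VR + T2) − Y(T2) = [Y(2D + T2) − Y(T2)] + [Y(2D + VR + T2) − Y(2D + T2)].

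The first bracket is the effect of a first-trimester 2D visit. The second is what 3D VR adds to it. Y(2D + T2) is observed in neither arm, so randomisation identifies only the sum.

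**Step 3. Labels against design.**

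| Place | Contrast named | Matches Step 2? |
|---|---|---|
| Study design; arm description in abstract Methods | 2D plus 3D VR added | yes |
| Discussion, paragraph on the clinician's point of view | first plus second trimester versus second trimester only | yes |
| Discussion, last sentence | adding first-trimester ultrasound | yes |
| Abstract Methods, comparison sentence | 3D VR versus usual care | no |
| Primary objective; primary outcome | 3D VR added to second-trimester 2D | no |
| Secondary outcomes | cost-effectiveness of 3D VR | no |
| Sample size, 70% rate | 3D VR plus second-trimester 2D | no |
| Discussion, closing paragraph | randomisation shows 3D VR's value against first-trimester 2D | no |

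**Step 4. What can be learned about 3D VR itself.** Outcome measurements plans a comparison of first-trimester 2D with 3D VR detection. It is made within the intervention arm, in the same fetuses, by examiners masked to each other until they agree. It is informative but not randomised, and each modality comes with its own examiner. It covers detection only. Quality of life and cost follow one visit and one agreed result, so the paired readings cannot divide them.

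**Step 5. Size of that comparison.** With the plan's 2800 participants and 7.5% prevalence, and 1:1 allocation assumed (the ratio is not stated), the intervention arm holds 2800 × 0.075 / 2 = 105 affected pregnancies. For a small paired difference, the 95% half-width is about 1.96 × √(d/105), where d is the assumed share of affected fetuses on which the two readings disagree:

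- d = 5%: 1.96 × √(0.05/105) = 4.3 points
- d = 10%: 1.96 × √(0.10/105) = 6.0 points
- d = 20%: 1.96 × √(0.20/105) = 8.5 points

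The values of d are assumptions, since the article gives none. The figure of 2800 serves here only to count affected pregnancies; this point does not depend on how it was derived.

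**The case against.** Three replies have force.

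First, the package is not hidden. Several places in the article describe it correctly, and because the 3D volumes are acquired at the same visit, 3D VR ultrasound could be a loose name for that visit. This stands in part: the text is inconsistent rather than wrong throughout. The shorthand reading fails in the closing Discussion, however. There, regular first-trimester 2D is the comparator, so it cannot also be part of what 3D VR means.

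Second, the comparison of 2D with 3D VR is already planned with masked readers. This stands. A reader might infer that the trial says nothing about 3D VR against first-trimester 2D, and the document does not support that. The choice of paired test can be left to the analysis plan.

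Third, the value of 3D VR goes beyond detection. Participants cannot see the 2D scan, and questionnaires ask parents and ultrasonographers about 3D VR. This also stands, and that evidence should be kept. It is descriptive, though. The planned participant comparison sets first-trimester 3D VR against second-trimester 2D, so modality and gestational age differ together.

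**Conclusion.** The point holds as one of labelling and conclusion. The randomised detection, quality-of-life and cost contrasts are effects of an added first-trimester 2D plus 3D VR examination. The claim that randomisation shows the desktop's value against first-trimester 2D is wrong for this design. The adoption statement for the new modality would not follow from a cost or quality-of-life benefit. The trial still answers a useful question about the combined examination.

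The share of any benefit due to 3D VR cannot be calculated from the document. A reader might infer that essentially all of the assumed 5-point gain comes from 2D, because the sample size section quotes 62.5% for first-trimester 3D VR against 61% (high risk) or 63% (low risk) for 2D: 62.5 − 61 = +1.5 and 62.5 − 63 = −0.5 points. The document does not support this. The rates come from different studies and populations. The same section also gives 18.2% to 71.8% for first-trimester 2D, which would put the difference anywhere from 62.5 − 71.8 = −9.3 to 62.5 − 18.2 = +44.3 points. Above all, these are stand-alone rates. The gain over the second-trimester scan depends on which anomalies each technique finds that the later scan misses, and stand-alone rates do not show that.

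The conclusion rests on the arm descriptions as published, with no first-trimester anomaly scan in usual care.

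**What to change.** 1. Name the combined first-trimester 2D plus 3D VR examination in the abstract's comparison sentence, the primary objective, the primary outcome, the 70% assumption, and the randomised quality-of-life and cost outcomes.
2. Base any claim that 3D VR detects more than first-trimester 2D on the within-arm comparison already planned. Use the findings of examiners A and B as recorded before agreement, and analyse them as paired data.
3. Keep the 3D VR perception questionnaires, reported as descriptive evidence.
4. Reword the closing Discussion so that a cost or quality-of-life benefit supports the combined first-trimester examination and not 3D VR specifically, and withdraw the claim that randomisation isolates the desktop's value.

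No new arm, data or change of care is needed, provided that each examiner's findings are stored before agreement. The price is a weaker claim for 3D VR: its advantage in detection would rest on a non-randomised comparison in about 105 affected pregnancies.
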